## Abstract

**Background:**

Nepal is on track to achieve MDG 5 but there is a huge sub-national disparity with existing high maternal mortality in western and hilly regions. The national priority is to reduce this disparity to achieve the goal at sub-national level. Evidences from developing countries show that increasing utilization of skilled attendant at birth is an important indicator for reducing maternal death. Further, there is a very low utilization during childbirth in western and hilly regions of Nepal which clearly depicts the barriers in utilization of skilled birth attendants. So, there is a need to overcome the identified barriers to increase the utilization thereby decreasing the maternal mortality. The hypothesis of this study is that through a package of interventions the utilization of skilled birth attendants will be increased and hence improve maternal health in Nepal.

**Method/Design:**

This study involves a cluster randomized controlled trial involving approximately 5000 pregnant women in 36 clusters. The 18 intervention clusters will receive the following interventions: i) mobilization of family support for pregnant women to reach the health facility, ii) availability of emergency funds for institutional childbirth, iii) availability of transport options to reach a health facility for childbirth, iv) training to health workers on communication skills, v) security provisions for SBAs to reach services 24/24 through community mobilization; 18 control clusters will not receive the intervention package. The final evaluation of the intervention is planned to be completed by October 2014. Primary study output of this study is utilization of SBA services. Secondary study outputs measure the uptake of antenatal care, post natal checkup for mother and baby, availability of transportation for childbirth, operation of emergency fund, improved reception of women at health services, and improved physical security of SBAs.

**Discussion:**

The intervention package is designed to increase the utilization of skilled birth attendants by overcoming the barriers related to awareness, finance, transport, security etc. If proven effective, the Ministry of Health has committed to scale up the intervention package throughout the country.

**Trial registration number:**

ISRCTN78892490.

## Background

Millennium development goals for the improvement of maternal health has shown suboptimal achievements in less than one fourth of countries where it is on track to reduce maternal mortality ratios (MMR) by 3/4^th^ (below 139/100000 live births) [1]. Only 16 of 68 countries are on track to achieve 2/3^rd^ reduction in under-five mortality by 2015 [2,3]. Increasing skilled attendant at birth is an important indicator for ensuring better maternal, child and neonatal health [4].

Nepal is making considerable progress in achieving Millennium Development Goals (MDG) 4 and 5 [1,3,5]. However, progress is uneven at sub-national level, between developmental and ecological regions, and in populations of different socio-economic status [6,7]. The national average of Infant Mortality Rate (IMR) per thousand live births is 48, but mid-western and far-western districts have 58 and 65 respectively. Likewise,mountain districts have the higher IMR (73) as compared to hill and terai districts (50 and 53) as per Nepal Demographic and Health Survey (NDHS) 2011 [8].Similar patterns are observed for MMR [9].

Despite a decrease in maternal mortality (770 in 1990 to 170 in 2010), [10] the underlying causes of maternal deaths remain of serious concern. An analysis of maternal deaths [1] reveals that nearly 83% of all maternal death is attributable to direct causes: the three main causes being post-partum hemorrhage (32%), hypertensive disorders during pregnancy (25%) and abortion (13%) [11]. Two third of infant deaths occur during the neonatal period [12]. Without improved availability and utilization of skilled birth attendant’s (SBAs) to address the direct causes of maternal deaths, further reduction in maternal and neonatal mortality is extremely unlikely. Amidst low SBA service coverage at the time of birth (28.8%) against the target to be achieved by the year 2010 (50%) and 2015 (60%) [13] women are still facing barriers in utilization of SBA services in Nepal. Research is needed to explore [1] the approach that will be cost effective and scalable to overcome the barriers to utilization of skill birth attendant services in Nepal.

### Efforts of national health system for maternal and child health improvement

In response to the need for accelerated actions to reach the desired reductions in maternal and newborn mortality, the government of Nepal (GoN) has devised several policy strategies and programs [14]. The National Health Policy (NHP) formulated in 1991 with the objective of enhancing the health status of rural population extends the primary health care system with the intention of increased access to modern medical facilities and trained health care providers.The subsequent health plans were based on the NHP and focused on strengthening neonatal, child and maternal health in Nepal. These include the Eighth Health Plan (1992–1997), the Ninth Health Plan (1997–2002), Tenth Five Year Plan (2002–2007), Three Year Interim Plans (2008–11, 2011–13) and the Second Long Term Health Plan (SLTHP) (1997–2017). The Three year interim plans aimed to provide free essential health care services for all citizens and the safe delivery incentive programme to accelerate the country’s progress towards achieving Millennium Development Goals 4 and 5 [15,16]. In these plans, achieving health results in women, children and vulnerable, marginalized, disadvantaged populations, as well as those living in hard to reach areas have been prioritized. The primary healthcare approach is central to the delivery of services [8].

The Safe Delivery Incentive Programme (SDIP), started in 2005, is central to government’s effort to improve maternal health. It aims to increase coverage of skilled birth attendance and also to contribute towards poverty reduction by preventing death and disability [17,18]. The SDIP was developed to help households overcome financial barriers to accessing maternity care. According to the revised policy guidelines, the SDIP provides: Women giving birth at eligible government health institutions (hospital, primary health care centre, or health post), medical colleges, mission hospitals and NGO-run hospitals receive a fixed sum of 1,500 NRs ( 20 $) in mountain areas, 1,000 NRs (12 $) in hill areas, and 500 NRs (6$) in the Tarai [19]. But, failure to pay the financial incentives to the women on time in many districts has resulted in low acceptance of the offer of the cash incentive. Consequently, low SBA coverage continues despite the financial incentives [20].

The GoN has endorsed a SBA policy in 2006 within the framework of the Safe Motherhood Policy 1998, and aims to increase service coverage to 60% by the year 2015 [21]. While the international target of SBA coverage is 90%, the target set by Nepal is in line with the WHO target for the countries with high levels of maternal mortality [21,22].

The progress in meeting this target, however, is slow, as SBA coverage has reached only 28.8% by 2010 [23]. This coverage accounts for service provided by ‘any’ kind of trained health professionals, many of which do not meet the strict criteria set by the SBA policy of Nepal [21] This SBA coverage would mainly refer to this mix of health professionals who may or may not be trained as SBAs. This is to happen unless SBA training to the health professionals is expanded quickly and in massive scale.

The government has deployed three major strategies; promoting birth preparedness and complication readiness, institutional childbirth, and expansion of 24-hour emergency obstetric care through the Safe Motherhood and Neonatal Health Long Term Health Plan (SMNHLTP 2006–2017). The SMNHLTP also includes an increased focus on other areas like the importance of addressing neonatal health as an integral part of safe motherhood programming, SBA policy, health sector reform initiatives, legalization of abortion and integration of abortion into the safe motherhood umbrella, prevention of mother to child transmission and emphasis on needs of poor and disadvantaged women [17].

In view of the low coverage of skilled birth attendance in Nepal, the Nepal Public Health Foundation baseline survey explores the barriers to seeking care with skilled attendants for childbirth care [24-27]. The findings showed that the cost of institutional birth, including the cost of transport, unavailability of transportation systems, insecurity of SBAs at health facilities discourage utilization of SBA services by women [28].

It is to be noted that even in terms of child birth assistance from a health personnel, Nepal ranks lower in South Asia. While Nepal and Pakistan have similar coverage (19%) ranking the second lowest, Bangladesh has lowest 13% and Sri Lanka has the highest 96% of births delivery attended by health personnel [8].

Our project baseline during April to December 2012 in Bajhang, Dailekh and Kanchanpur districts of Mid and Far Western Development region in collaboration with GoN and financial and technical support form WHO Geneva reported first ANC coverage of 88% while 4^th^ and more ANC visit of 65% in average. Only the half of the respondents (52%) knew about danger signs during pregnancy and delivery and 19% of them had faced complications during last delivery.

Our survey reported, 45% of births were assisted by SBA/THW which ranges from a high of (64%) in Kanchanpur and a low of (33%) in Bajhang. Which is low as compared to MDG target to scale up SBA coverage to 60% by 2015 [13]. This suggests additional efforts are required in scaling up skilled birth attendants in Nepal. This requires innovative intervention that uniquely address identified barriers in receiving care. Distance to reach health facility, lack of transportation means to reach the health facility, lack of information about the availability of services in health facilities were the identified barriers.

Amidst of possibilities and challenges in SBA service scale up, Nepal Public Health Foundation (NPHF) [24] has taken initiative and has been conducting a study on “Overcoming Barriers to Scaling Skilled Birth Attendants Utilization in Improving Maternal, Newborn and Child health in Nepal” as a three-year implementation research project with support from WHO-HQ, Geneva. The overall aim of the implementation research is to increase SBA service utilization by identifying the barriers related to service users and health systems regarding the utilization of skilled birth attendants and implementing a package of interventions to address these barriers.

### Hypothesis

It is hypothesized that through a package of interventions which includes activities to increase family support for pregnant women to reach health facility, make available funds to remove financial barriers faced by families for using institutional childbirth care, make available transport options to reach a health facility for childbirth, improving providers’ communication skills, and reduce security problems of SBAs so that care can be available 24/7 will lead to increased utilization of the services of a skilled birth attendant and subsequently improvements in maternal, newborn and child health in districts of Far and Mid West Nepal.

### Study objectives

#### **
*Primary research objectives*
**

The primary objective of this study is to increase the utilization of SBA services for childbirth.

### Secondary research objectives

1. To increase the utilization of four antenatal care visits by pregnant women and postnatal care services by mothers and babies.

2. To evaluate the effectiveness of the proposed implementation package in increasing SBA service utilization for childbirth care.

3. To assess the feasibility and scalability of the implementation package in other districts of Nepal.

## Methods/Design

### Study population

The intervention is being implemented in three districts of mid and far-western Nepal. Among them, one district is located in the mountains (Bajhang), one in a hilly zone (Dailekh) and the other in the plain terai (Kanchanpur) zone. Bajhang, Dailekh and Kanchanpur respectively have 48, 54 and 20 Village Development Committees (VDCs). The VDCs are the basic politico-administrative unit of Nepal which is further divided into nine smaller units called Wards having an average of 150 households (less in mountains and more in Terai) [29]. Each VDC consists of at least one health institution [17,30]. There are about 4000 VDCs in Nepal, out of which about 215 have Primary Health Care Centres, 699 have health posts (HP) and 3100 have sub health posts (SHP). According to the Nepal SBA policy, the health posts serve as the first contact birthing center for institutional birth and all the SHPs are being upgraded to HPs.

### Study design

The implementation research underway is to test the impact of interventions designed to address the main barriers to utilization of SBA services at birth identified in the baseline study. The study design is a cluster randomized controlled trial. The three districts (Bajhang, Dailekh and Kanchanpur) were the three strata and the VDCs from each stratum serve as clusters which were allocated for intervention and control by *randomization*. A baseline survey was conducted in 2011 in all 50 VDCs of the three districts. All women with under-5 children from each VDCs were included.

The three districts of Far and Mid-west Nepal represent three ecological zones –- Kanchanpur is Terai or a lowland belt stretching east to west in the south; Dailekh is Hills; and Bhajang is a mountainous areas. Selection of three districts was based on ecology with low human development index. The population inhabiting these districts is varied, representing different ethnic groups [31]. Terai district is mainly inhabited by aboriginal population of Nepal the Tharus; the mid hills by Kshetri and Bahun (Aryan upper cast but lower economic status). The mountain district has predominantly Mongoloid populations. These districts have lower indicators with respect to education, health and economic development.

The implementation of intervention covers 36 of the 50 VDCs of the three districts (22 VDCs of Bajhang, 10 VDCs of Dailekh and 4 VDCs of Kanchanpur (see table in Figure 1). VDCs having a rate of utilization of SBA at birth higher than the national target of 60% were excluded from the intervention. In order to have an even number of clusters, one more VDC with coverage of 57% was excluded.

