### Sample size estimate

The study includes all pregnant women in the 36 VDCs. It is estimated that at least 110 births per year will occur in each VDC and that the proportion of births assisted by a SBA is 36% [7]. The sample size was estimated assuming that the intervention and control groups and the unmatched clusters were of approximately equal size. A value of k -the between-cluster coefficient of variation – to be equal was estimated in the intervention and control groups. All estimates are based on a two-tailed 5% significance level. The value of k is likely to be 0.25 on the basis of estimates of the SBA utilization rate according to the baseline survey [24]. Hence, It was estimated that on at least 110 pregnant women in each cluster with 36 clusters would be required for the period of one year to detect a 10% difference in SBA utilization rate with 80% power and 95% confidence level.

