### Project time line

Intervention preparation: October, 2012

Formation of steering committee, preparation for trainings: November to January, 2013

Meeting and training: February, 2013

System of transportation and Emergency fund establishment:February to April, 2013

Intervention:May, 2013 to April, 2014

Evaluation of project: May to October, 2014

The evaluation of the impact of intervention will be done using multiple methods. Both the qualitative and quantitative methods will be used in evaluation. End line survey to determine the effects of the interventions will be done with key process indicators. This will include questionnaire surveys with 5000 women in 36 VDCs in three districts.Health workers, female community health volunteers, youth group members, health facility management committee members will be interviewed.

The instruments used for the base line survey will be used for the evaluation of outcome. Necessary modifications will be made to the instruments.Data will be entered in Epi data and imported to SPSS for analysis. Results from the bivariate and multivariate analysis will be compared with the baseline results. Intervention and control VDCs will be compared to identify any difference in the outcome variables to find out the association of the intervention components for possible change. Test of significance will be done at 5% significance level using appropriate statistical test.

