### Analysis strategies

Data will be double entered into EpiData 3.1, validated using Epi Info data compare, and will be transferred to SPSS 16 for analysis. The findings from quantitative tool will be presented in tabular and graphical forms. To control for more than one confounding variable multivariate logistic regression model will be applied. For statistical inference of the result, a confidence level of 95% is set. For the analysis process of qualitative data collected form FGD, the transcription of taped FGD session will be typed and reviewed thoroughly then translated in English language by field coordinators. The content of transcription will then be labeled as per the domain of analysis.

Missing data will be characterized in terms of the degree and patterns of missing data. For imputation of missing value of categorical variables, the frequency distribution will be used as the basis for randomly generating a value for each observation lacking a response. For example, if education was measured in three categories -- “less than high school” (25% of complete data cases), “completed high school” (40%), or “more than high school” (35%) -- then for each observation with education missing, a random number between 0 and 1 will be drawn from a uniform distribution and the missing value replaced with “less than high school” if the random number is less than or equal to 0.25, “completed high school” if the number is greater than 0.25 but less than or equal to 0.65, or “more than high school” if greater than 0.65. For imputation of numerical variable regression method is used.

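### The stated arm comparison names neither the district strata nor baseline VDC coverage as model terms, although the design supplies both and, on the protocol's own inputs, power is about 73% rather than 80%

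*Protocol article*

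**What the plan says.** **Design.** The Study design section makes district the stratum: "The three districts (Bajhang, Dailekh and Kanchanpur) were the three strata and the VDCs from each stratum serve as clusters". The 36 study VDCs are 22 in Bajhang, 10 in Dailekh and 4 in Kanchanpur, with 18 per arm. All 50 VDCs were surveyed at baseline. VDCs with SBA use above 60%, and one more at 57%, were left out, so coverage was known VDC by VDC. Ethical considerations records that baseline findings were shared with communities before randomisation.

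**Baseline spread.** The Background reports that "45% of births were assisted by SBA/THW which ranges from a high of (64%) in Kanchanpur and a low of (33%) in Bajhang".

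**Analysis.** Analysis strategies says: "To control for more than one confounding variable multivariate logistic regression model will be applied". The confounders are not named. Project time line gives baseline its only stated role: "Results from the bivariate and multivariate analysis will be compared with the baseline results". It adds that intervention and control VDCs will be compared with a suitable test at the 5% level.

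**Sample size.** The calculation treats the clusters as unmatched, with k equal in the two groups, and sets out "to detect a 10% difference in SBA utilization rate with 80% power and 95% confidence level".

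**The concern.** The randomisation supplies the first covariate, district. The baseline survey supplies a second, VDC-level coverage, measured before allocation. The text gives covariates the task of controlling confounding, which is the reasoning of an observational study. It gives baseline the task of a before-and-after comparison, which does not adjust the contrast between arms. As written, the analysis does not follow from the design.

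Two things are at stake. The first is precision: most of the variance lies between VDCs, so interviewing more women in each VDC barely helps, and explaining VDC differences is the cheap remedy. The second is discretion: if the confounders are chosen after the endline data are seen, so is the primary estimate, and a commitment to scale up nationally depends on it.

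Kanchanpur adds to this. At about 310 women per VDC, its four VDCs hold 4 × 310 = 1,240 of 22 × 110 + 10 × 110 + 4 × 310 = 4,760 women. That is 26% of the women in 11% of the clusters. A woman-level model without these terms is therefore sensitive to which of those four VDCs fell in which arm.

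**Working it through.** **Inputs, all from Sample size estimate unless noted.** Control proportion: "the proportion of births assisted by a SBA is 36" per cent. Cluster size: "at least 110 births per year will occur in each VDC", so m = 110. Difference: 10%, read as 10 percentage points (36% to 46%). k = 0.25, equal in both arms. Test: "All estimates are based on a two-tailed 5% significance level". Target power 80%. Clusters: 18 per arm (Abstract).

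**Step 1: the protocol's own figure.** For unmatched clusters with equal k (Hayes–Bennett), clusters per arm are

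c = 1 + (1.96 + 0.84)² × V / (p0 − p1)², where V = [p0(1−p0) + p1(1−p1)]/m + k²(p0² + p1²).

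- Within-VDC part: (0.2304 + 0.2484)/110 = 0.4788/110 = 0.00435.
- Between-VDC part: 0.0625 × (0.1296 + 0.2116) = 0.0625 × 0.3412 = 0.02133.
- V = 0.02568. The between-VDC share is 0.02133/0.02568 = 83%.
- c = 21.15, so 22 per arm or 44 clusters. The stated 36 is not reproduced.
- Power with 18 per arm: Φ(√(17 × 0.01/0.02568) − 1.96) = Φ(0.613) = 73.0%. A noncentral t calculation also gives 73.0%.

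One alternative reading does reach 36. With a common between-cluster SD of 0.25 × 0.36 = 0.09 in both arms, V = 0.00435 + 2 × 0.0081 = 0.02055, c = 17.1 and power is 82%. A design-effect calculation with continuity correction also rounds up to 18 per arm (17.5). The common-SD reading conflicts with the statement that k is equal in the two groups.

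**Step 2: what the two terms could recover.** Let R be the share of between-VDC variance explained by district and baseline coverage. Replace the between-VDC part by (1 − R) × 0.02133. R is not in the documents, so the table shows a range.

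| R (assumed) | V | SE relative to R = 0 | Clusters per arm for 80% | Power, 18 per arm |
|---|---|---|---|---|
| 0 | 0.02568 | 1.00 | 21.2 | 73% |
| 0.10 | 0.02355 | 0.96 | 19.5 | 77% |
| 0.20 | 0.02141 | 0.91 | 17.8 | 80% |
| 0.25 | 0.02035 | 0.89 | 17.0 | 82% |
| 0.50 | 0.01502 | 0.76 | 12.8 | 92% |

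The terms cost two degrees of freedom for district and one for baseline, leaving 36 − 5 = 31. A t calculation with 31 df agrees with these powers to within 0.3 points.

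**Step 3: how much could district alone explain?** This depends on what k measures. If k = 0.25 is across all VDCs, its variance at 36% is 0.09² = 0.0081. Assumed district means of 33/38/45%, weighted 22/10/4, give a between-district variance of 0.00155, or 19% of it. Means of 33/45/55% give 0.00604, or 75%. If k is already within district, the district gain is counted in the 73% and only baseline coverage can add to it. The article does not say which applies.

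**The case against.** **Silence is not omission.** A reader might infer that the analysis ignores district and baseline. The text does not support that: the confounders are unnamed, so neither is ruled out, and an analysis plan not shown may list them. This stands, and the point is limited to what the article specifies. It remains a point because the article does describe its analysis and assigns covariates and baseline other roles.

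**The district range does not describe the trial clusters.** A reader might take 33% to 64% as the spread among the study VDCs. Every retained VDC is at or below 60%, so, on the same measure, Kanchanpur's four cannot average 64%. The range must predate the exclusions, and the spread among the 36 is narrower. For the same reason, a rerun at 45% vs 55% is not supported: 45% is a survey average not shown to be after exclusions, and the planning rate is 36%.

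**Direction of the error.** A reader might conclude that intervals will be too wide. That holds only if the analysis respects VDC clustering. A logistic model with no VDC term would tend to err the other way, with standard errors too small. The 73% and the gains belong to a cluster-respecting analysis.

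**Baseline is an imperfect predictor.** The reported measure is births assisted by SBA/THW, among women with children under five, so some births may be several years old. The documents give no baseline-to-endline correlation. This stands and is why R is only assumed.

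**The shortfall depends on the equal-k reading.** True, but that is what the article states.

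**Conclusion.** The point holds as one of specification. Allocation was within three district strata and VDC-level baseline coverage was available beforehand, yet neither is named as a term in the arm comparison. On the stated inputs with equal k, power is about 73% against a target of 80%, and 83% of the variance lies between VDCs. Explaining about 20% of that between-VDC part would restore 80% power with the existing 36 clusters; 25% and 50% would give about 82% and 92%.

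The size of the gain is illustrative. It rests on an assumed R, on the unstated meaning of k and on an analysis that respects clustering. The documents do not establish that power has been lost by a fixed amount. They do show that a design-based model is available at almost no cost and has not been fixed.

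**What to change.** State in the protocol or analysis plan, before endline data are seen:

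1. The primary arm comparison respects VDC clustering, by a VDC-level regression of endline SBA proportion or by a mixed or GEE logistic model with a small-sample correction.
2. It includes arm, district (three strata) and baseline VDC SBA coverage, with the baseline measure defined (SBA or SBA/THW).
3. ANC and PNC use the same model with their own VDC baseline, where measured.
4. Models with other covariates are sensitivity analyses.
5. Whether k = 0.25 is within district or across all VDCs, with the power statement reconciled to it. Baseline data can show how much variance lies between districts among the 36 VDCs.

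Cost: analysis wording and three degrees of freedom (31 remain). No new data are needed.
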